## Abstract

**Background:**

In recent years, advancements in cancer treatment have enabled cancer cell inhibition, leading to improved patient outcomes. However, the side effects of chemotherapy, especially leukopenia, impact patients’ ability to tolerate their treatments and affect their quality of life. Traditional Chinese medicine is thought to provide complementary cancer treatment to improve the quality of life and prolong survival time among patients with cancer.

**Objective:**

This study aims to evaluate the effectiveness of Chinese herbal medicine (CHM) as a complementary treatment for neutropenia prevention and immunity modulation during chemotherapy in patients with breast cancer.

**Methods:**

We will conduct a real-world pragmatic clinical trial to evaluate the effectiveness of CHM as a supplementary therapy to prevent neutropenia in patients with breast cancer undergoing chemotherapy. Patients will be classified into CHM or non-CHM groups based on whether they received CHM during chemotherapy. Using generalized estimating equations or repeated measures ANOVA, we will assess differences in white blood cell counts, absolute neutrophil counts, immune cells, and programmed cell death protein 1 (PD-1) expression levels between the 2 groups.

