### Sample Size Estimation

The sample size calculation was based on the mean and SD of the amount of CD4+ between control and treatment groups based on the published literature [19]. By setting the effect size as 0.5, the sample size of each group was estimated as 64 to achieve a power of 0.80 at a significance level of .05 using G*Power software (version 3.1; Heinrich-Heine-Universität Düsseldorf). After accounting for an anticipated dropout rate of 10%, the final sample size was determined to be 70 in each group.

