### Exclusion Criteria

Patients who will not be able to complete the chemotherapy and follow-up procedures based on oncologists’ experience before grouping, those who receive other medication, and those with an Eastern Cooperative Oncology Group score of 3-4 will be excluded from the study.

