### Study Design

This study is a real-world pragmatic clinical trial conducted at the Hualien Tzu Chi Hospital in Taiwan. Patients with breast cancer scheduled to receive chemotherapy for their cancer treatment will be recruited as per the flowchart shown in Figure 1. Patients willing to receive CHM during chemotherapy are allocated to the CHM group, whereas those in the non-CHM group will not receive CHM.

To evaluate the effectiveness of CHM, the number of WBCs, the ANC, and the use of G-CSF in patients will be measured. The following questionnaires in Taiwanese will be used: (1) the Brief Fatigue Inventory—Taiwanese Version, (2) the World Health Organization Quality of Life-BREF, (3) the National Cancer Institute-Common Terminology Criteria for Adverse Events & Patient Reported Outcomes, and (4) the body constitution questionnaire. In addition, blood samples will be collected and analyzed for immune profiles and programmed cell death protein 1 (PD-1) expression. Generally, visit 1 represents the first collection of questionnaires and blood samples before the first chemotherapy session. Following the chemotherapy regimen, the first 4 rounds of chemotherapy will be performed every 3 weeks with 3 visits (visits 2-4). Subsequently, 12 rounds of chemotherapy will be performed once per week with another 4 visits (visits 5-8, 3 weeks per visit). Patients will be followed up within 1 month of undergoing chemotherapy. Patients in the CHM group will receive complementary CHM treatment after the first chemotherapy session.

The clinical data will be extracted from the medical history system. The questionnaires will be coded and transformed into numerical values (eg, 5=very satisfied or none, 4=satisfied or light, 3=no change or intermediate, 2=unsatisfied or severe, and 1=very unsatisfied or none) to facilitate statistical analysis. Immune profiles will be analyzed using flow cytometry. The data monitoring committee, clinical trial center of Hualien Tzu Chi Hospital, is independent from the funder and competing interests. The SPIRIT (Standard Protocol Items: Recommendation for Interventional Trials) 2013 checklist is provided in Multimedia Appendix 1 [20].

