### Safety Assessments

All adverse events (AEs) will be recorded throughout the study. In cases where AEs are caused by chemotherapy or CHM intervention, prompt measures will be taken to address those AEs. If needed, participants will be withdrawn from the study. Continuous monitoring of the participant’s blood, liver, and kidney functions, body weight, and vital signs will be performed throughout the study. The possible side effects associated with CHM are listed in Table 1.

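### The abstract groups patients by CHM actually received and the Methods by willingness at Week 0; the analysis section does not say which grouping the main comparison uses

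*Protocol article*

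**What the plan says.** The protocol article gives two definitions of the groups.

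- **Abstract, Methods:** "Patients will be classified into CHM or non-CHM groups based on whether they received CHM during chemotherapy". The sentence that follows applies the generalized estimating equations or repeated measures ANOVA to these two groups.
- **Study Design:** "Patients willing to receive CHM during chemotherapy are allocated to the CHM group, whereas those in the non-CHM group will not receive CHM". Table 2 ticks allocation at Week 0, ahead of Visit 1, and Visit 1 precedes the first chemotherapy session. The Exclusion Criteria refer to the oncologists' "experience before grouping", which also treats grouping as a baseline step.

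On timing, Study Design says: "Patients in the CHM group will receive complementary CHM treatment after the first chemotherapy session". The section on chemotherapy and CHM administration words the start differently and ties it to the first round of chemotherapy.

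Statistical Analysis repeats the between-group comparison and plans adjustment for age and other factors. It does not say which definition forms the groups, or how a patient whose uptake differs from the allocation is counted.

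**The concern.** Group membership is the exposure in this study, so every between-group result depends on it. Willingness at Week 0 is known before any chemotherapy toxicity. Receipt of CHM during chemotherapy is known only afterwards.

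Two kinds of patient are classified differently under the two rules:

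1. A willing patient who never starts CHM is in the CHM group by allocation and in the non-CHM group as received.
2. An unwilling patient who starts CHM later is in the non-CHM group by allocation and in the CHM group as received.

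If early toxicity prompts either departure, the as-received groups are partly sorted by early blood counts or symptoms, which are related to the later counts being compared. Never-starters who did badly and are counted as non-CHM make CHM look better. Late starters who did badly and are counted as CHM make it look worse. Adjusting for age and other baseline characteristics does not undo sorting on an event that happens after baseline.

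**Working it through.** **1. The plan's own figure.** Sample Size Estimation says "By setting the effect size as 0.5, the sample size of each group was estimated as 64" and "to achieve a power of 0.80 at a significance level of .05". A two-sided two-sample t test (noncentral t) with d = 0.5 and alpha = 0.05 needs n = 64 per group, with power 0.801. The stated 64 reproduces. For 10% dropout, 64/0.9 = 71.1, which rounds up to 72 against the stated 70; that gap does not matter here. The figure used below is the design effect of 0.5 SD.

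**2. Where the rules agree.** If every willing patient takes CHM and nobody else does, both rules give the same groups and the bias is zero.

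**3. Simulation with no true effect.** From the document: 64 per group by willingness, a two-sided 5% test and a continuous outcome (the primary outcome is immune cell numbers). Assumed, because the document gives neither: the fraction f of one group that departs from its allocation, and the correlation rho between early status E and the later outcome Y. The model is Y = rho·E + √(1 − rho²)·e, with E and e standard normal, so Y has SD 1. The departing patients are those with the worst E. Higher Y is taken as better. There were 4,000 runs per cell. Entries are the mean difference CHM minus non-CHM in SD, with the type I error in brackets.

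Willing patients who never start, counted as non-CHM:

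| f | rho 0.3 | rho 0.5 | rho 0.7 |
|---|---|---|---|
| 10% | +0.102 (8.6%) | +0.163 (14.0%) | +0.234 (24.7%) |
| 20% | +0.175 (16.4%) | +0.294 (36.4%) | +0.403 (62.2%) |
| 30% | +0.223 (22.2%) | +0.373 (51.9%) | +0.522 (83.9%) |

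Unwilling patients who start later, counted as CHM:

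| f | rho 0.3 | rho 0.5 | rho 0.7 |
|---|---|---|---|
| 10% | −0.093 (8.0%) | −0.164 (15.0%) | −0.230 (25.4%) |
| 20% | −0.176 (16.2%) | −0.288 (36.1%) | −0.405 (62.3%) |
| 30% | −0.229 (22.8%) | −0.375 (53.8%) | −0.524 (84.3%) |

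With the same data grouped by allocation, the mean difference stays within 0.005 SD of zero and the type I error is 4.3% to 5.6% in all 18 cells.

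**4. Hand check of one cell (never-starters, f = 20%, rho = 0.5).** Of 64 willing patients, 13 move, so q = 13/64 = 0.203, z = −0.831 and φ(z) = 0.2826.

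- Mean E of those who move: −0.2826/0.203 = −1.391. Mean E of those who stay: 0.2826/0.797 = 0.355.
- As-received CHM mean: 0.5 × 0.355 = 0.177.
- As-received non-CHM mean: 13 × 0.5 × (−1.391)/(64 + 13) = −0.117.
- Difference: 0.177 + 0.117 ≈ 0.295, against 0.294 simulated.

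**5. Sign.** The two routes mirror each other. If equal fractions departed by both routes for the same reason, the two biases would cancel. The net sign therefore depends on which route dominates, and the document does not say.

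**The case against.** The strongest defence is that the body of the Methods is consistent. Willingness, the Week 0 tick and exclusions judged before grouping all describe one baseline rule, and only a condensed abstract sentence departs from it. Study Design also plans that the non-CHM group receives no CHM, in which case the wordings coincide. How departures are counted is often left to a full protocol or SAP, and neither is shown. This limits the point but does not remove it. The abstract links the as-received rule directly to the between-group analysis, and Statistical Analysis does not settle the matter, so two incompatible definitions stand in one document.

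Three stronger readings are tempting, and the text does not support them.

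- **That the bias favours CHM.** Late starters counted as CHM push the other way, and nothing in the document says which departure is commoner.
- **That patients who start and soon stop would move to non-CHM.** The abstract sets no minimum duration. Such a patient has received CHM and stays in the CHM group. Only never-starters and late starters change group. CHM also begins around the first chemotherapy session, so the time for toxicity to prevent a first dose may be short. The 30% never-starter row may well be pessimistic.
- **That the Safety Assessments sentence "If needed, participants will be withdrawn from the study" adds to the misclassification.** Withdrawal after an adverse event creates missing data. It moves nobody between groups.

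**Conclusion.** The point stands as a contradiction over the study's central variable, where one of the two stated rules is post-baseline. It does not show that the planned analysis is biased. The risk is conditional on patients departing from their allocation and on early toxicity driving those departures.

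Under assumed switching of 10% to 30% and correlations of 0.3 to 0.7, as-received grouping produces a false difference of about 0.1 to 0.5 SD in either direction. At the upper end that is as large as the 0.5 the study is designed to detect. Type I error ranges from 8% to 84% in place of 5%. The switching rates and correlations are assumptions, each table lets only one route operate, and the actual size and sign cannot be derived from the document.

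Grouping at Week 0 avoids this particular bias. It does not remove confounding from self-selection, because patients choose their own group.

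**What to change.** - **Abstract, Methods:** replace the as-received sentence with the allocation rule already in Study Design.
- **Statistical Analysis:** state that the main comparison uses the group recorded at Week 0 allocation for every enrolled patient, whether or not CHM is later started, stopped or added. Label the as-received comparison a sensitivity analysis.
- **Data collection:** state that outcome data continue to be collected after CHM stops unless consent is withdrawn, so that patients can be analysed in their allocated group.
- **Timing:** reconcile the statements on when CHM starts in Study Design and in the section on chemotherapy and CHM administration.

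The cost is a few sentences; the allocation step already exists. The statistical price is some dilution of any real effect if many patients switch, and the sensitivity analysis gives the as-received result to set beside the main one.

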**Results:**

This study was approved by the research ethics committee of Hualien Tzu Chi Hospital (IRB 110-168-A). The enrollment process began in September 2021 and will stop in December 2024. A total of 140 patients will be recruited. Data cleaning and analysis are expected to finish in the middle of 2025.

**Conclusions:**

Traditional Chinese medicine is the most commonly used complementary medicine, and it has been reported to significantly alleviate chemotherapy-related side effects. This study’s findings may contribute to developing effective interventions targeting chemotherapy-related neutropenia among patients with breast cancer in clinical practice.

**Trial Registration:**

International Traditional Medicine Clinical Trial Registry ITMCTR2023000054; https://tinyurl.com/yc353hes

**International Registered Report Identifier (IRRID):**

DERR1-10.2196/55662

## Introduction

Chemotherapy-induced neutropenia (CIN) is a common complication and represents the most severe hematological toxicity associated with cancer chemotherapy. This condition has several complications, including severe infections, aggressive hospital management, life-threatening morbidity, and mortality [1]. Briefly, CIN is generally characterized by a decreased absolute neutrophil count (ANC) of <2000 cells/mm^3^ in the peripheral blood and is classified into 4 grades according to the National Cancer Institute Common Toxicity Criteria. The classifications of CIN severity are as follows: (1) grade 1 with an ANC of 1500-2000 cells/mm^3^, (2) grade 2 with an ANC of 1000-1500 cells/mm^3^, (3) grade 3 with an ANC of 500-1000 cells/mm^3^, and (4) grade 4 with an ANC <500 cells/mm^3^. The current standard treatment for CIN is the use of granulocyte colony-stimulating factor (G-CSF) to attenuate white blood cell (WBC) count and ANC [2]. The use of prophylactic G-CSF also improves patients’ quality of life (QoL) [3].

Breast cancer, particularly triple-negative breast cancer (TNBC), encompasses a heterogeneous group of cancer cells, and its treatment remains challenging. In patients with neoadjuvant chemotherapy (NAC)–treated TNBC with residual disease, higher stromal tumor–infiltrating lymphocytes (sTILs) in the resected tumor conferred an improved prognosis [4]. Moreover, higher pre-NAC sTILs and elevated pre-NAC expression of cytotoxic T-cell markers and cytokines are associated with better pathological complete response and overall survival rates [5]. sTILs, with a published cutoff of 30%, are the most widely studied marker of antitumor immunity. Besides, these sTILs could be used to predict improved response to NAC and better prognosis in the context of residual disease of patients lacking pathologic complete response. However, the mechanisms underlying the immunomodulatory effects of chemotherapy on sTILs and the influence of chemotherapy on the tumor-immune microenvironment are poorly understood.

NAC alters both tumor-infiltrating and peripheral immune cells in patients with breast cancer. The reduced levels of signal transducer and activator of transcription 1 (STAT1), activator protein-1 transcription factor subunit (Jun), and nuclear factor kappa B (NF-κB) in B cells, cytotoxic T cells, and natural killer (NK) cells, respectively, from the pretreatment stage to the mid- and posttreatment stages indicated that NAC could inhibit the activation, proliferation, and differentiation of these cells. Moreover, B cell signatures detected using single-cell RNA sequencing are significantly associated with improved survival in patients with breast cancer [6]. However, a significant decrease in the fraction of B cells and C-X-C chemokine receptor type 4, which are involved in maintaining B cell population and function, was reported during and after NAC in peripheral blood mononuclear cells (PBMCs). A previous study also demonstrated that decreased neutrophil levels correlated with a poor response to NAC [7]. High levels of systemic cluster of differentiation 8 (CD8+) cytotoxic T cells are associated with improved survival in patients with metastatic breast cancer [8]. Furthermore, the expression of cytotoxic genes in PBMCs, as opposed to tumor-immune microenvironment, may be invasive biomarkers of persistent micrometastatic disease, ultimately leading to recurrence [9]. Accordingly, lower neutrophil density in patients with breast cancer is associated with metastasis or poor prognosis.

In addition, the percentages of CD3+CD4+CD25+CD127-FoxP3+ regulatory T cells, intermediate monocytes (CD14++CD16+), and HLA-DR-CD11b+CD33+CD15+ myeloid-derived suppressor cells were reported to be significantly higher in the PBMCs of patients with breast cancer. After a single round of NAC, the intensity of CD56 expression in NK cells was significantly increased, as was the percentage of activating receptors NKp44, NKp30, and 2B4 and inhibitory receptors leukocyte-associated immunoglobulin-like receptor (LAIR) and NKG2A. The activity, rather than the proportion of NK cells, is affected [10].

In addition to conventional therapy, an increasing number of patients with breast cancer are seeking Chinese herbal medicine (CHM), as indicated by web-based surveys exploring the perspectives of patients with breast cancer concerning complementary and alternative medicine. CHM has been reported as one of the most common complementary treatments for patients with breast cancer, associated with a possible reduction in the risk of complications, including alopecia [11], neuropathy [12], and fatigue [13], as well as with an improvement in the overall QoL [14]. Moreover, the results based on claims data suggest that using CHM in combination with conventional therapy may improve the overall survival rate by 45% [15]. However, whether CHM as a complementary therapy can alleviate myelosuppression and neutropenia remains controversial. Previous studies have demonstrated that *shenqi fuzheng* injection [16] and *xihuang* pill or capsule [17] could regulate immunity and reduce tumor markers. Nevertheless, other placebo-controlled randomized controlled trials have stated that using CHM as a complementary therapy did not prevent myelosuppression in patients with breast cancer treated with adjuvant chemotherapy [18].

Understanding how NAC reshapes antitumor immunity, both in the tumor and peripheral compartments, is essential; however, the immunomodulatory effects of NAC are still unclear. The Chinese herbs frequently used in cancer treatment, including *huang qi, dang gui, huang qin, bai zhu*, and *nuzhenzi* (Table 1), could regulate immunity, but how they affect immune cell profiles is mainly unknown. Given that some CHM has been suggested to have immune regulatory effects, we hypothesized that CHM, as a supplementary therapy during chemotherapy, could lower the risk of neutropenia in patients with breast cancer. Accordingly, we are conducting a real-world pragmatic clinical trial to evaluate the effectiveness of CHM as a complementary treatment for neutropenia prevention and immune modulation during chemotherapy in patients with breast cancer.

**Table 1 table1:** Candidate Chinese herbal medicines in this study.

Pharmaceutical Latin	Chinese name	Applications or effects	Possible side effects
*Astragalus membranaceus*	*Huang qi*	Enhance immune system, heart function, and blood sugar control	Rash, itching, runny nose, nausea, and diarrhea
*Angelica sinensis*	*Dang gui*	Heart diseases, menopausal and menstrual symptoms, high blood pressure, and inflammation	Fatigue, allergic reactions, and should not be prescribed to pregnant women and children
*Scutellaria baicalensis Georgi*	*Huang qin*	Diarrhea, insomnia, dysentery, high blood pressure, hemorrhaging, respiratory infections, and inflammation	Gastric discomfort, nausea and vomiting, and diuresis
*Atractylodes* *macrocephala*	*Bai zhu*	Antiulcer, enhance immunity, and antioxidant	Decrease blood pressure and hypoglycemia
*Fructus ligustri lucidi*	*Nuzhenzi*	Optic neuritis, leukopenia, chronic hepatitis, hyperlipidemia, coronary heart disease, and hypertension	Dizziness and diarrhea

## Methods

### Participant Recruitment

Participants are being recruited from the Hualien Tzu Chi Hospital. Recruitment began on September 12, 2021, and is expected to continue until December 2024. We expect to complete the study in the middle of 2024.

### Ethical Considerations

This study was approved by the research ethics committee of Hualien Tzu Chi Hospital (IRB 110-168-A), and informed consent will be collected from all study participants. The information of patients will be deidentified, and each visit will be compensated for US $16. This study was registered on the International Traditional Medicine Clinical Trial Registry website (ITMCTR2023000054).

### Sample Size Estimation

The sample size calculation was based on the mean and SD of the amount of CD4+ between control and treatment groups based on the published literature [19]. By setting the effect size as 0.5, the sample size of each group was estimated as 64 to achieve a power of 0.80 at a significance level of .05 using G*Power software (version 3.1; Heinrich-Heine-Universität Düsseldorf). After accounting for an anticipated dropout rate of 10%, the final sample size was determined to be 70 in each group.

### Inclusion Criteria

Patients aged 20 years and older, with a histologically confirmed diagnosis of breast cancer before the initiation of chemotherapy, are considered eligible for this study.

### Exclusion Criteria

Patients who will not be able to complete the chemotherapy and follow-up procedures based on oncologists’ experience before grouping, those who receive other medication, and those with an Eastern Cooperative Oncology Group score of 3-4 will be excluded from the study.

### Study Design

This study is a real-world pragmatic clinical trial conducted at the Hualien Tzu Chi Hospital in Taiwan. Patients with breast cancer scheduled to receive chemotherapy for their cancer treatment will be recruited as per the flowchart shown in Figure 1. Patients willing to receive CHM during chemotherapy are allocated to the CHM group, whereas those in the non-CHM group will not receive CHM.

To evaluate the effectiveness of CHM, the number of WBCs, the ANC, and the use of G-CSF in patients will be measured. The following questionnaires in Taiwanese will be used: (1) the Brief Fatigue Inventory—Taiwanese Version, (2) the World Health Organization Quality of Life-BREF, (3) the National Cancer Institute-Common Terminology Criteria for Adverse Events & Patient Reported Outcomes, and (4) the body constitution questionnaire. In addition, blood samples will be collected and analyzed for immune profiles and programmed cell death protein 1 (PD-1) expression. Generally, visit 1 represents the first collection of questionnaires and blood samples before the first chemotherapy session. Following the chemotherapy regimen, the first 4 rounds of chemotherapy will be performed every 3 weeks with 3 visits (visits 2-4). Subsequently, 12 rounds of chemotherapy will be performed once per week with another 4 visits (visits 5-8, 3 weeks per visit). Patients will be followed up within 1 month of undergoing chemotherapy. Patients in the CHM group will receive complementary CHM treatment after the first chemotherapy session.

The clinical data will be extracted from the medical history system. The questionnaires will be coded and transformed into numerical values (eg, 5=very satisfied or none, 4=satisfied or light, 3=no change or intermediate, 2=unsatisfied or severe, and 1=very unsatisfied or none) to facilitate statistical analysis. Immune profiles will be analyzed using flow cytometry. The data monitoring committee, clinical trial center of Hualien Tzu Chi Hospital, is independent from the funder and competing interests. The SPIRIT (Standard Protocol Items: Recommendation for Interventional Trials) 2013 checklist is provided in Multimedia Appendix 1 [20].

